#### Intervention Period

Participants from the control group will perform conventional hypertension monitoring using paper logbooks. Participants from the intervention group will use the app for 3 months, periodically registering the values of blood pressure, weight, height, sleep quality, waist circumference, mood, and heartbeats, among others. Health professionals from the health centers will assist the participants by using the website dashboard to monitor and interact with their patients. Professionals’ performance will not be evaluated, but we will ask them to participate by communicating with patients weekly on the platform. We will use all the data recorded by patients and health professionals during the intervention in the final analysis of results, especially the measurements of blood pressure and frequency of physical activity.

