#### Statistical and Qualitative Analysis

Our expectation for the primary outcome is the reduction and stabilization of blood pressure. For the secondary outcome, we hope for acceptance of the eHealth platform and improvements in treatment adherence, physical activities, and dietary intake. A priori levels will be set according to the assessment tool and the expected outcome. The acceptance of the eHealth platform will consider good scores obtained in the analysis of usage logs and questionnaires of engagement, SUS, and TAM. Improved adherence to treatment will consider MBG questionnaire scores measured before and after the intervention. For the analysis of physical activities and dietary intake, a binary outcome will consider whether the patient has adequate levels, diagnosed according to the SISVAN’s questionnaire and standards.

For qualitative data, we will use Minayo’s guidelines [30]. Numeric data will be analyzed with statistical software SPSS 22 (IBM Corp, Armonk, New York). We will calculate the measures of central tendency and dispersion of the quantitative variables, and we will use the Kolmogorov-Smirnov test to verify normality. Basic quantitative data will be determined by mean, standard deviation, and median. Categorical data will be determined by simple frequency. Blood pressure data will be analyzed with the paired *t* test. Either the paired *t* test (parametric) or the Wilcoxon test (nonparametric) may be applied to compare other quantitative variables before and after the intervention. To assess treatment adherence, physical activity, and dietary intake after intervention, we will apply the Chi-square test while considering the app use as the dependent variable; the independent variables will be treatment adherence, physical activity, and dietary intake. For the MBG questionnaire, we will apply the Mann-Whitney test to compare the score between the groups before and after the intervention. The same test may be used to compare diastolic and systolic blood pressure measurements between the preintervention and postintervention groups. We will consider a 95% confidence interval (*P*<.05).

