To evaluate the findings’ heterogeneity (primary and secondary outcomes), we will apply a statistical technique to verify whether the differences observed in the results can be explained by chance. We will apply the Chi-square test with a significance level of *P*<.10. The magnitude of heterogeneity will be assessed by calculating the I^2^ value, which ranges from 0% to 100%. An I^2^ greater than 50% indicates substantial heterogeneity, and an I^2^ above 75% indicates considerable heterogeneity. For the evaluation of heterogeneity, we will consider the demographic and socioeconomic variables. In the presence of heterogeneity, we will investigate its causes through sensitivity analysis. In the sensitivity analysis, the form of data analysis varies, to identify the impact of this change on the results. All analysis techniques can be adjusted or modified, if required, by the characteristics of the collected data. If feasible, we also intend to analyze the results with logistic regression of preintervention and postintervention data. In this case, the dependent variable will consider the base category *whether* [user] *used the app*, related to independent, categorized, and continuous variables of interest such as sociodemographic variables and the expected secondary outcomes.

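### The optional regression of app use on the secondary outcomes takes in platform acceptance, which controls cannot have, so it cannot be estimated as worded

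*Protocol article*

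**What the plan says.** All of this is in the protocol article.

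- **Status of the regression** (Statistical and Qualitative Analysis): "If feasible, we also intend to analyze the results with logistic regression of preintervention and postintervention data".
- **Dependent variable** (same section): "the dependent variable will consider the base category *whether* [user] *used the app". Only the intervention group receives the app, so this is in effect group membership.
- **Predictors** (same section): "related to independent, categorized, and continuous variables of interest such as sociodemographic variables and the expected secondary outcomes". The list is given by example and no number is fixed.
- **Secondary outcomes** (same section): "For the secondary outcome, we hope for acceptance of the eHealth platform and improvements in treatment adherence, physical activities, and dietary intake". Acceptance is to be judged by "good scores obtained in the analysis of usage logs and questionnaires of engagement, SUS, and TAM".
- **Controls** (Intervention Period): "Participants from the control group will perform conventional hypertension monitoring using paper logbooks". Under Study Population and Sample, a patient whose phone cannot run the app goes to the control group.
- **Chi-square analysis** (Statistical and Qualitative Analysis), also with app use as the dependent variable: "the independent variables will be treatment adherence, physical activity, and dietary intake". Acceptance is not among them.

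**The concern.** One of the outcomes named as a predictor exists only because a patient had the app. Acceptance cannot help to explain who used the app, since having an acceptance value at all already answers that question.

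Allocation follows phone ownership, without randomization, so adjusted comparisons carry real weight here. This regression is the only multivariable outcome analysis that the section describes. If it cannot run as worded, the predictors will be chosen after the data are seen, and the section's general permission to modify techniques would allow that. A second worry is that even without acceptance, the open list could produce a model that is large for the sample and odds ratios that are too far from 1.

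**Working it through.** **1. The plan's sample size.** Inputs from Study Population and Sample: 80% against 40%, 95% confidence, 80% power. Two-sided testing is assumed.

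- Uncorrected: n = [1.96·√(2·0.6·0.4) + 0.8416·√(0.8·0.2 + 0.4·0.6)]² / 0.4² = (1.358 + 0.532)² / 0.16 = 22.3, so 23.
- Continuity-corrected: (22.3/4)·[1 + √(1 + 4/(22.3·0.4))]² = 27.1, so 28 per group, as stated.
- Allowance for losses: 28 × 1.20 = 33.6, so 34, as stated.

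The range below is therefore 28 (evaluable) to 34 (enrolled) per group.

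**2. Acceptance as a predictor.** There are two ways to handle controls without a value.

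- *Complete cases.* All controls drop out. What remains is 28 or 34 app users, and the dependent variable takes one value. No logistic model can be estimated.
- *Controls scored as zero.* Every control has 0 and every user a positive score. A very negative intercept with a steep slope pushes the fitted probabilities towards 0 and 1, so the likelihood has no finite maximum. A trial fit (user scores assumed to have mean 70 and SD 10) did not converge. Standard errors were above 20,000 for the intercept and above 120,000 for the slope at n = 28, and larger at n = 34. Any strictly positive user scores would give the same result.

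**3. The model without acceptance.** Three outcomes remain: adherence, activity and diet. The number of sociodemographic terms is an assumption. Three is the set named for the propensity score (age, gender, socioeconomic status). Six would arise if the questionnaire items were added or coded in categories. The dependent variable is group, so the smaller class is 28 to 34.

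- 6 parameters: 28/6 = 4.7 to 34/6 = 5.7 patients per parameter.
- 9 parameters: 28/9 = 3.1 to 34/9 = 3.8.

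**4. What that does to the estimates.** There were 1,000 simulated trials per setting. Assumptions: three binary outcomes, each 80% against 40% (the primary-outcome rates, borrowed), and unrelated covariates. The true log odds ratio is ln[(0.8/0.2)/(0.4/0.6)] = ln 6 = 1.792. Failed or unstable fits are counted separately and left out of the mean.

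| Parameters | n per group | Failed or unstable | Mean log OR | Inflation |
|---|---|---|---|---|
| 3 | 28 | 1.9% | 1.971 | 10% |
| 3 | 34 | 0.7% | 1.971 | 10% |
| 6 | 28 | 2.8% | 2.179 | 22% |
| 6 | 34 | 0.8% | 2.143 | 20% |
| 9 | 28 | 6.2% | 2.440 | 36% |
| 9 | 34 | 2.4% | 2.283 | 27% |

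Inflation is the mean divided by 1.792, minus 1. With 6 to 9 parameters, a true odds ratio of 6 would appear as about exp(2.143) = 8.5 to exp(2.440) = 11.5.

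**The case against.** **The analysis is conditional and its list is illustrative.** A sensible analyst would leave out a predictor that is absent in one group, and the chi-square sentence, with the same dependent variable, already does so. This stands as a reason for low severity and shows that the authors probably had three outcomes in mind. It does not make the regression sentence right: it names the secondary outcomes without exception, acceptance is one of them, and feasibility has no stated criterion.

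**Controls might have acceptance data.** The Postintervention Period section describes a meeting of all participants and does not limit the engagement, TAM and SUS questionnaires to the intervention group. That acceptance exists only in app users is therefore an inference. It is a strong one: patients who did not have the app leave no usage logs, and their ratings of a platform they never used would mean little.

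**A reader might infer that the remaining predictor list is too long.** The protocol contains no such list, and nothing says that every questionnaire item enters one model. The smallest set that can be assembled from named variables has 6 parameters, and that model could nearly always be fitted.

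**A reader might also infer a small-sample problem from false-positive rates.** With nine unrelated predictors, simulation gives a 39% to 41% chance of at least one P<.05. Ordinary multiplicity alone gives 1 − 0.95⁹ = 37% at any sample size, so this says little about 28 to 34 patients per group.

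**Nor is this the plan's only multivariable element.** Study Population and Sample also names a propensity score.

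**Conclusion.** The point holds in a limited form. As worded, the regression includes a predictor with no meaningful value in controls, and that model cannot be estimated under either way of handling them. This rests on reading the secondary outcomes as the section itself lists them, and on controls not having used the platform.

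Once acceptance is removed, what remains is a weakness of degree: log odds ratios inflated by about 20% to 36%, with 0.8% to 6.2% of fits failing or unstable. Those figures depend on an assumed 6 to 9 parameters and on borrowed 80% and 40% rates. The documents do not support saying that the trimmed model would fail, or that a fixed list is too long.

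Severity is minor to moderate. The analysis is optional, the primary comparison does not depend on it, and the repair is small.

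**What to change.** - State that between-group models use only outcomes defined in both groups: adherence, physical activity and diet, as in the chi-square analysis.
- Analyse acceptance (logs, engagement, SUS, TAM) within the app group only, and say so where the postintervention questionnaires are listed.
- Replace the regression of app use with one small model per outcome. The outcome is the dependent variable. The predictors are allocated group, the outcome's baseline value where collected (the MBG score is listed before and after the intervention), and the propensity score already planned. This estimates the group difference directly.

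This makes about three parameters. For a binary outcome, the limiting count becomes the rarer result. At an assumed 80% and 40%, that is 28 × 0.2 + 28 × 0.6 = 22.4, or 22.4/3 = 7.5 patients per parameter. With 34 per group it is 27.2/3 = 9.1. This is better than 3.1 to 5.7, though still modest.

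The cost is two or three sentences in the analysis section. The small downside is that fewer covariates are entered individually.

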## Results

The project was funded at the end of 2018. We will develop the software between 2019 and 2020, and we will enroll patients between 2020 and 2021. We expect to submit the first results for publication in 2020. As the final technological product, we will offer an innovative and technological eHealth platform to the public sector. The transfer of technology from the academic environment to the public sector is a strategy to invigorate efforts and enable improved health conditions to the population.

## Discussion

The expected results may contribute to improving the quality of life of patients with arterial hypertension. Using eHealth technology will allow a better understanding of the importance of permanent health care. Furthermore, it will provide encouragement for health monitoring and risk assessment, favoring behavior changes toward healthier habits [31-33]. In public and primary health, the technology that favors disease control also helps reduce complications and, consequently, treatment costs [34,35]. The eHealth platform encourages the adaptation of medical assistance to facilitate the incorporation of technology into patient monitoring, especially for those living in rural areas or regions of difficult access [36,37]. Nevertheless, introducing the use of technology may simplify health information records and communication between patients and professionals [38]. The health database created may further benefit and integrate Brazilian systems such as the SIS-Hiperdia.

## Appendix

Multimedia Appendix 1 CONSORT-EHEALTH checklist (V 1.6.1).

## Abbreviations

eHealth: electronic health
MBG: Martín-Bayarre-Grau
SIS-Hiperdia: Brazilian Clinical Management System of Arterial Hypertension and Diabetes Mellitus
SISVAN: Dietary intake questionnaire by the Brazilian Food and Nutrition Surveillance System
SUS: System Usability Scale
TAM: technology acceptance model
